### Sample Size

The primary outcome of this trial will be the extent to which clinicians involve their patients in the decision-making process, as scored using the OPTION-5 instrument [30,61]. A ≥10-point improvement in the OPTION-5 score is considered clinically relevant and significant, given the relatively limited time investment of the participants. For instance, a >10-point OPTION-5 score indicates 2 out of 5 items improving from moderate effort (2 points) to skilled effort (3 points) or 1 item improving from minimal effort (1 point) to skilled effort (3 points).

A preintervention mean score of 38 is assumed for our sample, which was measured in a former implementation project involving 6 outpatient breast cancer teams [32]. This is a high baseline score compared with other studies in general [56] and for oncology [9,11,57]. A total sample size in a 2-sided *Z* test for 2 means of 72 patients will be calculated based on an increase in the OPTION-5 score from 38 before implementation to 48 after implementation, with an SD of 13 in both groups, achieving a 90.38% power at the 5% significance level [13,32,56]. We will expand the sample size to 100 clinicians to account for possible failed recordings and dropouts of clinicians. A subanalysis will be performed to evaluate whether the results for palliative decisions, that is, patients who are palliatively treated (both tumor targeted and non–tumor targeted), are similar to those for the group with curative treatment intentions.

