## Methods

### Trial Design

This multicenter, single-blinded randomized clinical trial was designed and will be reported in accordance with the CONSORT (Consolidated Standards of Reporting Trials) guidelines [47]. The trial addresses the effect of SDM interventions in real-life clinician-patient consultations on the extent to which clinicians involve their patients in the decision-making process. The design is unpaired, meaning that patients are only audiotaped once, either before or after the intervention. In the control group, the clinicians will not receive the SDM intervention until the trial period has finished. The trial will include different oncology clinicians, diagnoses, hospitals, and decisions to investigate applications in a range of oncological diagnoses, including patients in palliative care.

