### Study Conduct

When joining the study, clinicians will complete a short questionnaire asking about their number of years of experience, former participation in SDM skills training (yes or no) during medical school or as part of continuous medical education, residency, profession, age, and gender. The diagnosis, gender, and age of the patients will be recorded by the clinician to gather the basic demographic data of the study sample.

A measurement involves recording ≥1 consultation relevant to a decision-making process of 1 patient only, with a questionnaire that measures patients’ perceived involvement in the decision-making process. The physicians and patients will be aware that consultations are being recorded. Each clinician will record the decision-making process for 3 different patients. By recording 2 consultations after the SDM intervention, with a time interval of 3 to 4 weeks between the recordings, the effectiveness of the SDM intervention for clinicians can be measured over time. The duration of the consultations and coaching sessions will be noted by the researcher ([name]) directly from the recordings. Clinicians will be instructed not to participate in educational activities related to patient-centered communication during the study. In addition, clinicians in the intervention group will be asked not to discuss the training contents or study-related information with participants in the control group. Once the final consultation is recorded, clinicians in the control group will receive the equivalent communication training. The period between each measurement will be 3 to 4 weeks, summing up to a total participation of approximately 8 weeks per clinician.

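### The sample size is counted in patients and then in clinicians, although clinicians are randomised and each contributes three recordings; the 90.38% power holds only for 72 different clinicians with one recording each

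*Protocol article*

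**What the plan says.** All references are to the protocol article.

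- **Sample Size.** The calculation is a two-sided Z "test for 2 means of 72 patients will be calculated based on an increase in the OPTION-5 score from 38 before implementation". The effect is a before-to-after change, "increase in the OPTION-5 score from 38 before implementation to 48 after implementation". The spread and the resulting power are given in these terms: "with an SD of 13 in both groups, achieving a 90.38% power at the 5% significance level". The next sentence changes the unit: "We will expand the sample size to 100 clinicians to account for possible failed recordings and dropouts of clinicians".
- **Randomization and Blinding.** Individual clinicians are allocated 1:1.
- **Outcomes.** The primary outcome, OPTION-5, rates the clinician's behaviour.
- **Study Conduct.** "Each clinician will record the decision-making process for 3 different patients". In the intervention arm, two of these recordings follow the training.
- **Comparator.** Control clinicians record two patients before the training is offered, and a third with it.
- **Trial Design.** "The design is unpaired, meaning that patients are only audiotaped once, either before or after the intervention".
- **Statistical Methods.** Mean differences with 95% CIs are planned, and a regression model for OPTION-5 to which unbalanced covariates are added. The section mentions neither a clinician effect nor correlation between recordings, and does not say which recordings form the primary contrast.

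**The concern.** Scores from the same clinician measure the same person's habits and cannot be presumed independent. The two-sample Z calculation assumes that every observation is independent. A total of 72 patients could mean 72 clinicians with one recording each, or far fewer clinicians with several each, and these designs carry different information. The move from 72 patients to 100 clinicians leaves the reader unsure which was sized.

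The term unpaired adds to the doubt. It is true of patients, who are each recorded once, but not of clinicians, who are the randomised unit and are measured three times. The before-after framing of the effect also differs from the randomised question, which is a comparison between arms.

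At stake are the meaning of the stated power, the number that counts as an adequate trial, and the validity of any test or interval that uses more than one recording per clinician. The last point applies equally to the patient questionnaires and to consultation duration.

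**Working it through.** **Inputs from the document:** difference 10 (38 to 48), SD 13 in both groups, two-sided alpha 0.05, total 72 (36 per group), expansion to 100 clinicians, three recordings per clinician.

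**Assumed:** the within-clinician ICC, which the document does not give. Values of 0.2, 0.3 and 0.5 are used to show a range.

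**Step 1: reproduce the stated power.** SE = 13 × √(2/36) = 3.064. Power = Φ(10/3.064 − 1.96) = Φ(1.304) = 90.38%. This matches exactly, so the arithmetic is right for 36 versus 36 independent observations.

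**Step 2: the 72 are clinicians with one recording each.** No clinician appears twice, so the ICC plays no part and power stays at 90.38%. With all 100 clinicians, SE = 13 × √(2/50) = 2.6 and power = Φ(10/2.6 − 1.96) = 97.0%. With 72 clinicians and two recordings each, correctly analysed, power is 98.8%, 98.2% and 96.5% at the three ICCs, and never below 90.38%.

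**Step 3: the 72 are recordings from 36 clinicians, two each.** The design effect is 1 + ICC, and power = Φ(10/(3.064 × √(1 + ICC)) − 1.96).

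**Step 4: two recordings per clinician pooled within each arm as if independent.** True two-sided alpha = 2 × [1 − Φ(1.96/√(1 + ICC))]. The CI has 1/√(1 + ICC) of its correct width.

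**Step 5: one recording before and one after in the same clinicians, analysed as unpaired.** The true variance of the difference is smaller by the factor (1 − ICC). The CI is therefore 1/√(1 − ICC) times the correct width, and true alpha = 2 × [1 − Φ(1.96/√(1 − ICC))].

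| Assumed ICC | Step 3: power | Step 4: alpha | Step 4: CI width ratio | Step 5: alpha | Step 5: CI width ratio |
|---|---|---|---|---|---|
| 0.2 | 84.6% | 7.4% | 0.91 | 2.8% | 1.12 |
| 0.3 | 81.7% | 8.6% | 0.88 | 1.9% | 1.20 |
| 0.5 | 76.0% | 11.0% | 0.82 | 0.6% | 1.41 |

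The direction of the error therefore depends on the contrast. Intervals are too narrow when recordings are pooled within an arm, correct with one recording per clinician, and too wide for an unpaired before-after comparison.

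**The case against.** The strongest reply is that the plan has a coherent reading under which nothing fails. The expansion to 100 is expressed in clinicians and justified partly by clinician dropout, and the randomisation section also speaks of about 100 participants. Read that way, the 72 are evaluable clinicians with one recording each, and the power is as stated. This stands, and it is why the point concerns the stated unit and not the number recruited.

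Second, the article does not say that recordings will be pooled or treated as independent. The regression model is unspecified, and its detail may lie in an analysis plan that is not shown. The Z test is named only for sizing, and the chi-square test is for categorical variables. A reader might infer that the planned tests and intervals are too narrow. The document does not support that, because it does not fix the contrast and the error can run either way.

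Third, a two-versus-two pooling between arms is not the documented comparison. On the Comparator section's account, it would need the control clinicians' baseline recording. This also stands, and the figures for that case show only what would happen if it were done.

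Fourth, unpaired is defined at patient level and is true there. Granted; it needs limiting, not withdrawing.

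None of this removes the change of unit between two adjacent sentences, or the use of an independent-samples calculation in patients for a trial that randomises and rates clinicians repeatedly. An unseen analysis plan could settle the model, but it would not correct the Sample Size text.

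**Conclusion.** The point holds as a fault in how the sample size and design are stated, with a conditional consequence for the analysis. The 90.38% is correct arithmetic for 72 independent observations and carries over to this trial only as 72 different clinicians with one recording each. If the same 72 came from 36 clinicians, power would be about 85%, 82% or 76% at an ICC of 0.2, 0.3 or 0.5. If two recordings per clinician were pooled within an arm as independent, the 5% test would run at about 7.4%, 8.6% or 11.0%. In an unpaired before-after contrast within clinicians, the test would instead be conservative. All of these shifts rest on an assumed ICC and on analyses that the document leaves open.

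A reader might also infer that the trial is too small. That is not shown: 72 evaluable clinicians give at least 90.38% at any ICC, and 100 are planned.

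**What to change.** 1. In Sample Size, restate the target as 72 evaluable clinicians, 36 per arm, for the between-arm contrast. Keep 100 randomised, which allows for a loss of 28 (28%).
2. Name the recording or recordings that form the primary contrast in each arm. If more than one per clinician is used, state the ICC assumed.
3. In Trial Design, say that unpaired refers to patients only and that clinicians are measured repeatedly.
4. In Statistical Methods, state that every analysis of OPTION-5, the patient questionnaires or duration that uses more than one recording per clinician will account for clinician. A random clinician intercept, GEE or clinician means would each serve.

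The cost is small: some rewording, a different procedure in the software already planned, and wider intervals wherever recordings would otherwise have been pooled. The recruitment target does not change.

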### Statistical Methods

All raters will use the OPTION-5 coding scheme, which has been refined for patients of oncology and vascular surgery [61,64]. The manual will be adjusted to be relevant to the oncology setting to increase raters’ agreement in scoring the audio recordings. All audio recordings will be scored independently by 2 raters blinded to the intervention using the OPTION-5 instrument. After the first 10 audio recordings, these scores will be compared, and the coding rules will be discussed to reach an agreement over the final score. Moreover, the personal feedback and coaching sessions with the first 10 clinicians will be discussed by the project team in which patients are involved, and the unweighted Cohen κ values will be calculated as a measure of the interrater agreement [65]. The OPTION-5 score will be converted from a 0- to 20-point scale into a 0% to 100% scale.

Descriptive statistics will be presented as percentages or means with SDs. Differences will be expressed as mean differences with 95% CIs. The Pearson chi-square statistic will be used to analyze the differences between categorical variables at *P*<.05. We will check whether previous training in communication skills, professional background, disease, duration of the consultation or consultations, hospital, age, and number of consultations are equally distributed between the study arms. If they are not equally distributed, they will be included in the regression model for the OPTION-5 score. We will also perform a subanalysis for palliative decisions to evaluate whether the effectiveness of the SDM intervention for these consultations is comparable with that for the entire group. Statistical analyses will be performed using SPSS Statistics (version 25; IBM Corporation).

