**Methods:**

This multicenter, single-blinded randomized clinical trial will be performed at 12 Dutch hospitals. Clinicians involved in decisions with oncology patients will be invited to participate in the study and allocated to the control or intervention group. All clinicians will record 3 decision-making processes with 3 different oncology patients. Clinicians in the intervention group will receive the following SDM intervention: completing e-learning, reflecting on feedback reports, performing a self-assessment and defining 1 to 3 personal learning questions, and participating in face-to-face coaching. Clinicians in the control group will not receive the SDM intervention until the end of the study. The primary outcome will be the extent to which clinicians involve their patients in the decision-making process, as scored using the Observing Patient Involvement–5 instrument. As secondary outcomes, patients will rate their perceived involvement in decision-making, and the duration of the consultations will be registered. All participating clinicians and their patients will receive information about the study and complete an informed consent form beforehand.

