### Outcomes

The primary outcome is the OPTION-5 instrument to rate the clinicians’ behavior in the decision-making process objectively, which will be performed by 2 of the 3 researchers ([name] and [name] and [name]) independently [30]. Each of the 5 items will be rated on a scale ranging from 0 (no effort made) to 4 (exemplary effort made).

As secondary outcomes, we will use subjective measures of SDM scored by the patients: the iSHARE, Control Preferences Scale (CPS), and the SDM Questionnaire–9 (SDM-Q-9) questionnaires.

The 15-item iSHARE questionnaire measures the perceived level of SDM during medical consultation or consultations; it was recently developed and has shown adequate content validity and comprehensibility [55]. It covers the entire SDM process rather than a single consultation and involves both clinician and patient behaviors. It is especially meant for the oncology setting, as definitions of SDM differ between health care settings [58]. The CPS has proven to be a clinically relevant, easily administered, valid, and reliable measure of preferred or experienced roles in decision-making among people with life-threatening illnesses [59]. The CPS comprises 1 question with 5 possible statements indicating the role of the clinician and patient in the decision-making process. The SDM-Q-9 comprises 9 statements. For each statement, patients rate the extent to which they *completely disagree* (0) to *completely agree* (5) on a 6-point Likert-type scale. The scores are added, multiplied by 20, and divided by 9 to provide a percentage of the maximum score, ranging from 0 (no SDM) to 100 (maximum level of SDM). If needed, a maximum of 2 missing items will be imputed with the mean of the items that are scored [60]. The duration and number of consultations are registered for each physician directly from the audiotaped consultation or consultations.

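### The primary OPTION-5 regression may adjust for duration and number of consultations measured after training, so it need not estimate the total effect of the training.

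*Protocol article*

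**What the plan says.** The Statistical Methods section names seven variables to be compared between arms: previous communication training, professional background, and whether "disease, duration of the consultation or consultations, hospital, age, and number of consultations are equally distributed between the study arms". The consequence is stated as a rule: "If they are not equally distributed, they will be included in the regression model for the OPTION-5 score". OPTION-5 is the primary outcome: "The primary outcome is the OPTION-5 instrument to rate the clinicians’ behavior in the decision-making process objectively".

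Elsewhere the article gives two of these variables a different role. The abstract's Methods paragraph puts duration in the secondary-outcome sentence: "As secondary outcomes, patients will rate their perceived involvement in decision-making, and the duration of the consultations will be registered". The Outcomes section adds: "The duration and number of consultations are registered for each physician directly from the audiotaped consultation or consultations". These are the recordings that are rated with OPTION-5.

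On timing, the Study Conduct section describes the intervention arm as follows: "By recording 2 consultations after the SDM intervention, with a time interval of 3 to 4 weeks between the recordings". Two of that arm's three recordings therefore follow the training. The first precedes it, because the feedback report and the coaching are built on it. The Statistical Methods section does not say which recording supplies the duration and number used in the balance check.

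**The concern.** The Objective section asks whether the training improves shared decision-making behaviour compared with standard practice. That is a total effect, and it includes any part that works through longer or additional consultations.

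Five of the seven variables are characteristics of the clinician, patient or site that the training cannot alter. Duration and number are different when they come from a post-training recording. The training teaches clinicians to raise options, discuss pros and cons and explore values, which could plausibly change how long a consultation takes. A measurement may also cover more than one consultation per patient, so number could change too.

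If such values enter the model, the treatment coefficient becomes the effect among consultations of equal length. The rule makes this worse, because it adjusts when the arms differ, and a difference caused by training is one way for them to differ. The definition of the primary estimate would then depend on what the training did to a secondary outcome.

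**Working it through.** **Step 1. Reproduce the design figure.** The Sample Size section assumes "an increase in the OPTION-5 score from 38 before implementation to 48 after implementation". Its other inputs are an SD of 13 per arm, a two-sided Z test at the 5% level and 72 in total, which is 36 per arm. The stated power is 90.38%.

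- SE = 13 × √(2/36) = 3.064
- 10/3.064 = 3.264
- Power = Φ(3.264 − 1.960) = 90.38%, as stated
- With 50 per arm (all 100 clinicians analysed), the same formula gives 97.0%.

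**Step 2. Effect of adjusting.** Let r be the within-arm correlation of duration with OPTION-5 and d the shift in duration caused by training, in SDs of duration. By the ANCOVA identity:

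adjusted effect = 10 − 13 × r × d

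The documents give neither r nor d. Assumed here: duration SD 10 min, r from 0.3 to 0.5, and an increase of 3 to 5 min, so d is 0.3 to 0.5.

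- Low corner: 13 × 0.3 × 0.3 = 1.17 points removed, 8.83 left.
- High corner: 13 × 0.5 × 0.5 = 3.25 points removed, 6.75 left.

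**Step 3. Power when adjustment occurs.** Adjustment also reduces the residual SD to 13 × √(1 − r²) and inflates the variance by 1 + d²/4, so SE = 13 × √(1 − r²) × √((2/n)(1 + d²/4)).

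| r | Increase | Effect left | Residual SD | Variance inflation | Power, 36 per arm | Power, 50 per arm |
|---|---|---|---|---|---|---|
| 0.3 | 3 min | 8.83 | 12.40 | 1.02 | 85% | 94% |
| 0.3 | 5 min | 8.05 | 12.40 | 1.06 | 76% | 88% |
| 0.5 | 3 min | 8.05 | 11.26 | 1.02 | 85% | 94% |
| 0.5 | 5 min | 6.75 | 11.26 | 1.06 | 69% | 83% |

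**Step 4. How often the rule would adjust.** Assume that the check on duration is a two-sided test at P<.05. The article states that level only for categorical variables. At 36 per arm:

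- 3 min: 0.3/√(2/36) = 1.27, so the probability is about 25%.
- 5 min: 0.5/√(2/36) = 2.12, so the probability is about 56%.

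With no shift in duration it is 5%.

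**Step 5. Simulation check.** With 10,000 runs at r = 0.4 and d = 0.5, the mean adjusted estimate was 7.45 (formula 7.4), with 71% power at 36 per arm if adjustment is always made. Averaged over the conditional rule, the estimate was 8.2 at 36 per arm and 7.8 at 50 per arm. With r = 0 or d = 0 it stayed at 10.

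**The case against.** The strongest defence is that the list may be meant as a baseline check. The first intervention-arm recording precedes training, so its duration and number cannot be effects of training, and most of the other listed items are baseline characteristics. Adjusting for that value would be harmless. This reading is possible, but no sentence in the article states it, and the rule as written admits post-training values.

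It may also be said that longer consultations give more room to score, so adjustment is fair. In a randomised comparison, extra time that the training brings about is part of its effect. The effect at equal length is a separate, exploratory question.

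Several stronger readings are tempting but not supported:

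- That both variables are declared outcomes. Only duration is named with the secondary outcomes. Number is registered in the Outcomes section without that label, and no figure is available for its effect.
- That the bias must run toward the null. This needs training to lengthen consultations and longer ones to score higher, and the article says neither. If training shortens consultations, the sign reverses. If duration is unchanged, there is no bias in expectation.
- That power falls to about 63%. That figure comes from a 7-point effect with the unadjusted SD of 13, which is not the adjusted model.
- That the primary estimate will certainly be distorted. Adjustment is conditional, the sample size rests on an unadjusted comparison of two means, and the article does not say that the regression replaces the unadjusted mean difference for the primary conclusion.

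**Conclusion.** The concern holds in a limited form. The article states a rule, so this is not detail left to an unseen analysis plan. The rule lets post-training duration and number of consultations into the OPTION-5 model, and for duration this conflicts with its place among the secondary outcomes. Where it operates, the model no longer estimates the total effect of training, and it is more likely to operate the more the training changes duration.

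The documents do not fix the size. Under the assumptions set out above, the loss is about 1.2 to 3.3 of the 10 points. Both the loss and the accompanying fall in power apply only when adjustment occurs. The direction depends on how training affects duration and how duration relates to the score.

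**What to change.** Remove post-training duration and post-training number of consultations from the covariate list of the primary OPTION-5 model, and compare both between arms as outcomes. Allow as covariates only variables fixed before training, named in advance. For duration and number this means at most the value from the pre-training recording. Outright deletion of the two items is not needed, because it would also bar that harmless value. Any model adjusted for post-training duration should be labelled an exploratory mediation analysis that does not support the primary conclusion.

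This takes a sentence or two in the Statistical Methods section and needs no additional data or participants.

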### Comparator

The time schedule for participants randomized to the control group is shown in Figure 1. They will first be asked to complete the recording of the decision-making process of 2 different patients before they are offered the intervention (including recording a third decision-making process). This will enable a comparison of their SDM behavior with participants who are exposed to the intervention. By offering the intervention to participants in the control group after the trial period, we will ensure that all participants in this trial have the opportunity to develop themselves in the field of SDM. To keep similar trial circumstances, the interval between these 3 recordings (3-4 weeks) will be similar to that of the intervention group.

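### Covariates enter the OPTION-5 regression only if they look unbalanced; the list omits the clinician's first OPTION-5 score and includes two variables the training can change

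*Protocol article*

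**What the plan says.** The Statistical Methods section names the variables whose balance will be checked: "previous training in communication skills, professional background, disease, duration of the consultation or consultations, hospital, age, and number of consultations". It then gives the rule: "If they are not equally distributed, they will be included in the regression model for the OPTION-5 score". The only criterion nearby is a Pearson chi-square at P<.05 for categorical variables. No threshold is given for continuous ones, and the terms of the regression itself are not set out.

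Other sections bear on what that regression could use:

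- Study Conduct: "Each clinician will record the decision-making process for 3 different patients". In the intervention arm two of the three follow the training ("By recording 2 consultations after the SDM intervention"), so one precedes it.
- Comparator: control clinicians "complete the recording of the decision-making process of 2 different patients before they are offered the intervention".
- Trial Design: "The design is unpaired, meaning that patients are only audiotaped once, either before or after the intervention". This describes patients. Under Randomization and Blinding, the unit allocated is the clinician, who is measured repeatedly.
- Sample Size: a two-sided Z test for two means, for an "increase in the OPTION-5 score from 38 before implementation to 48 after implementation", "with an SD of 13 in both groups".
- The Abstract lists consultation duration among the secondary outcomes, and the Outcomes section has duration and number of consultations taken from the recordings.

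**The concern.** The rule has three weaknesses.

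First, it makes the model depend on the observed data. Under randomisation, a difference between arms in a true baseline variable arises by chance. How visible that difference is says nothing about whether the variable predicts OPTION-5. With no stated criterion for age, duration or number of consultations, the analyst decides what counts as unequal after seeing the result.

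Second, the covariate most likely to be prognostic, the same clinician's untrained OPTION-5 score, is not among those listed. A chance difference in initial skill between arms would not be picked up by the check.

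Third, two listed variables are not baseline variables. Duration and number of consultations come from the recordings and could plausibly change because of the training. If the training lengthens consultations, the arms will differ in duration, the rule will admit it, and the adjusted estimate will no longer be the total effect of training.

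At stake are the credibility of an effect estimate whose model was not fixed in advance, its interpretation if a consequence of training is adjusted for, and some precision.

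**Working it through.** **Inputs from the article.** Difference 10 points (38 to 48), SD 13, two-sided 5% level, total 72, allocation 1:1 (36 per arm), 12 hospitals, expansion to 100 clinicians. The 72 is treated here as one follow-up score per clinician.

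**Input not in the article.** The correlation r between a clinician's first and follow-up OPTION-5 scores. It is assumed and shown over a range.

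**Step 1: the plan's own figure.** The standard error is 13 × √(2/36) = 3.064. Power is Φ(10/3.064 − 1.960) = Φ(1.304) = 90.38%. This matches the stated figure exactly, so the planned precision takes nothing from the first recording.

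**Step 2: adjustment for the first-recording score.** The residual SD becomes 13 × √(1 − r²), and the rest of the calculation is unchanged.

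| Assumed r | Variance removed (r²) | SE | Power at 72 | Total N for 90.38% |
|---|---|---|---|---|
| 0 | 0% | 3.064 | 90.4% | 72 |
| 0.1 | 1% | 3.049 | 90.7% | 72 |
| 0.2 | 4% | 3.002 | 91.5% | 70 |
| 0.3 | 9% | 2.923 | 92.8% | 66 |
| 0.4 | 16% | 2.808 | 94.5% | 62 |
| 0.5 | 25% | 2.654 | 96.5% | 54 |

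**Step 3: chance difference in initial skill.** With the same SD at the first recording, the difference between arms also has SE 3.064, so differences up to 1.96 × 3.064 = 6.0 points are ordinary. A 6-point difference moves the unadjusted estimate by r × 6: 0.6 points at r = 0.1, 1.8 at 0.3 and 3.0 at 0.5, against a target of 10.

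**Step 4: how often the rule would act by luck.** If all seven variables were tested independently at 5%, the chance of at least one flag is 1 − 0.95⁷ = 30.2%. This is illustrative: the article attaches 5% only to categorical variables, and the variables may be related. For hospital, 12 × 2 = 24 cells give an average expected count of 72/24 = 3.0 to 100/24 = 4.2, if clinicians are spread evenly. That is low for a Pearson chi-square.

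**Step 5: simulation of the rule.** There were 6,000 trials per scenario, with 36 per arm and seven independent candidates that training cannot affect, each tested at 5%. Candidates were either unrelated to the outcome or had a standardised coefficient of 0.2 each. The effect was 0 or 10/13 SD.

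| Quantity | Unadjusted | Imbalance rule | Prespecified first score |
|---|---|---|---|
| Type I error | 0.046–0.052 | 0.040–0.051 | 0.046–0.051 |
| Power, r = 0.3 | 0.90 | 0.89–0.90 | 0.92 |
| Power, r = 0.5 | 0.90 | 0.89–0.90 | 0.96 |

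The rule gains essentially nothing over no adjustment, and it does not inflate type I error for true baseline covariates.

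**Step 6: the post-randomisation variables.** The simulation does not cover these. If training changes mean duration by d, and OPTION-5 rises by b per unit of duration within arm, the duration-adjusted estimate is the total effect minus b × d. The article gives neither b nor d, so the shift cannot be sized. It is zero only if one of them is zero.

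**The case against.** A reader might infer that the plan never adjusts for the first-recording score. The article does not support that. It lists variables to be checked, not the base model, and a fuller plan that is not shown could include the score. What can be said is that the score is not in the named list.

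A reader might also infer that selecting on imbalance raises the false-positive rate, or that chance imbalance biases the result. Neither is shown. Simulated type I error was 0.040 to 0.051, and under randomisation the confidence interval already allows for chance imbalance.

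The precision argument rests on an assumed r. Each recording involves a different patient, and diagnoses and decisions vary, palliative ones included, so r may be low. At 0.1 the gain is negligible. Planned power of 90% is reached without adjustment, and if all 100 clinicians (50 per arm) were analysed it would be 97.0%.

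Finally, it is unclear whether the first recording precedes allocation, because the study-design figure is not available here. Clinicians are not blinded, and the Intervention section gives all participants a card with the SDM steps without saying when. A score recorded after allocation would be a less clean covariate.

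These points limit the size of the concern. They do not rescue the selection sentence, which is written out in full, or the presence of duration and number of consultations in its list.

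**Conclusion.** The point holds as a criticism of a stated rule. Covariates are chosen on observed imbalance, so the model is settled after the data are seen. The list leaves out the clinician's own first score and admits two variables that training may change, one of them a secondary outcome. The harm is discretion over the model, possible bias from adjusting for consequences of training, and lost precision.

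The lost precision is conditional on r: 0.3 percentage points of power at r = 0.1, 2.4 at 0.3 and 6.1 at 0.5, all at 72. The possible bias cannot be sized from the article. No inflation of type I error is claimed, nor that adjustment for the first score has been ruled out.

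**What to change.** Delete the sentence that selects covariates by imbalance, and keep the balance table as description only.

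Prespecify the primary model as OPTION-5 at the second recording on arm plus the clinician's first-recording OPTION-5 score. The second recording is the first after training in the intervention arm and the second untrained one in the control arm. It needs to be named because the Comparator section places the control arm's third recording within the offered intervention, whereas Study Conduct places control training after the final recording. The second recording is untrained in controls on either account.

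Limit further covariates to a few variables fixed before randomisation and named now, such as previous training and profession, whatever their observed balance. Exclude duration and number of consultations as covariates and report them as outcomes.

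Confirm that the first recording precedes allocation; if it does not, state that as a limitation of the adjusted analysis.

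The cost is a change of analysis wording and about one degree of freedom per added covariate. The recordings are already part of the design, so no extra data collection is needed.
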